### Study treatment

Based on the literature [16–18], and our pilot study [29], we decided to administer a single dose of tranexamic acid, corresponding to 20 mg/kg in 100 ml saline to all patients in the treatment group 1 at the beginning of the procedure. In the control group 2, we administer only 100 ml saline as placebo.

For prophylaxis of venous thromboembolism (according to the rules of our institution), the combination of mechanical device (graduated compression stockings) and pharmacologic agents (low-molecular weight heparin (LMWH)) in both treatment groups will be used. The prophylactic dose of LMWH is administered in the evening before the procedure, and the next dose at least 8 h after the procedure and then every evening at least till POD 7. Antibiotic prophylaxis is provided by a single dose of potent aminopenicillin as recommended by the antibiotic center: fluoroquinolone in patients with an allergy to aminopenicillin. During the procedure, the console time and weight of the prostate are monitored. Relevant concomitant care and interventions are permitted if necessary.

The surgical technique is standardized and has been described previously [30]. Standard robotic-assisted radical prostatectomy without pelvic lymphadenectomy using DaVinci Xi surgical system is performed. The dorsal vein complex (DVC) is sutured at the beginning of the procedure with two rounds of resorbable monofilament suture. To accelerate the return of continence, a modified Rocco stitch is performed in all patients. The anastomosis is performed by two tied V-loc stitches. No additional manipulation, such as fibrin glue or reinforcement with meshes, is allowed. Patients with rectal or bowel injury during the procedure will be excluded from evaluation.

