For 3 h after the procedure, patients of both groups will stay in the intermediate care unit; after moving to the standard ward, blood samples will be obtained. On POD 1, all the patients will start with mobilization and solid food intake. The volume of the fluids in the drain will be measured on postoperative day 1, and if the volume will not exceed 200 ml for 24 h, the drain will be extracted. If the volume is higher than 200 ml/24 h and the creatinine level in drain fluid exceeds 500 μmol/l, urinary leakage will be confirmed [31]. On POD 2, the patients will be released for home care with an indwelling permanent urinary catheter. On POD 7, the urinary catheter and skin sutures will be extracted, and the blood sampling and ultrasound of the lower abdomen will be performed. Three months after the procedure, a follow-up visit is scheduled. The evidence of complication and level of prostatic specific antigen (PSA) is monitored.

Upon completion in 200 patients, the statistical processing will be performed, and patients will be unblinded.

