### Data collection

A daily visit of the study patients will be made by clinical investigators or a delegated physician. All protocol-required information collected during the trial will be entered into the patient’s record form.

Patient identification on the case report form (CRF) is through their unique trial identifier, allocated at the time of recruitment. Data coding will be carried out at various stages during the study. The patient’s record form is subject to audit by the principal investigator (PI) and Institutional Review Board (IRB).

Preoperative data gathered include patient age, body mass index, American Society of Anesthesiologists physical status classification system score, and comorbidities. Intraoperative data to be collected include surgery duration (skin to skin), console time (console surgeon activity time), and weight of the prostate.

Laboratory tests will include blood cell count (BCC), hematocrit test, and plasmatic creatinine level at the beginning of the procedure, 3–6 h after the procedure, on POD 1, POD 2, and POD 7 in the morning.

The differences between the hematocrit and hemoglobin levels (eventually weighted for the grams of the prostatic tissue) and hemoglobin/creatinine ratios will be obtained.

The volume of the fluids in the drain will be measured on postoperative day 1, and if the volume does not exceed 200 ml for 24 h, the drain is extracted. If the volume will be higher than 200 ml/24 h and the creatinine level in the drain fluid exceeds 500 μmol/l, urinary leakage will be confirmed (29). Patients with confirmed urinary leakage or urinoma will be excluded from the evaluation.

Postoperative course assessments will include duration of intermediate/intensive care, hospital stay including readmissions for postoperative complications, reinterventions (reoperations, endoscopic and interventional radiology procedures), the reasons for readmissions, and transfusion rates. The patients will be seen by a clinical investigator 3 months after the surgery in an outpatient fashion. The evidence of complication and level of prostatic specific antigen (PSA) will be monitored. Upon completion of 200 patients, the statistical processing will be performed, and results will be unblinded.

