#### Adverse event reporting and harms

Adverse events (AE) reported by the patient or by the investigator will be recorded and scored according to the NCI Common Terminology Criteria for Adverse Events (CTCAE). If AE happen during the experimental treatment period, all the details will be notified in the CRF as the time of occurrence, clinical symptoms and signs, degree, duration, and causal relationship with the treatment. In case of serious adverse events (SAE), the investigator has to inform the PI within 2 h after finding the SAE at the latest. The investigator may stop immediately the treatment if it is considered in the best interest of the patient. The imputability of the SAE with the experimental must be established. SAE with a doubtful, possible, probable, or highly probable consequence of tranexamic acid administration will be considered as associated to it. If SAE are unexpected, they will be designed as suspected serious adverse reactions (SUSARs). In this case, the PI has to declare it to the ethical committee and IRB. This must occur not later than 15 days after the first knowledge of the SAE. In case of fatal or self-threatening cases, the delay will be reduced to a maximum of 7 days and 8 days supplementary for the report completion. Once a year, the PI will create a report with the complete list of SAE that could be associated to the experimental medication including expected and unexpected effects, and a precise and critical analysis of the safety of participants included in the study.

The IRB of the study will systematically meet every 12 months after the beginning of the trial and will decide whether or not to continue the study.

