### Primary and secondary endpoints

The primary endpoint is to analyze the effect of tranexamic acid on perioperative and postoperative blood loss in a randomized and prospective manner. A clinically significant difference between the groups on POD 1 is set to 10 g/l. The sample size was calculated for this setting.

The additional aim of the RARPEX trial is to analyze the effect of tranexamic acid on other postoperative complications: wound infection, intraabdominal collections, urinary leakage, delayed gastro-intestinal emptying, postoperative hemorrhage, pneumonia, and abdominal rupture, especially analyzing the incidence of cardiac events and venous thromboembolism (VTE) after the procedure (Table 1).

**Table 1 Tab1:** Clinical parameters and postoperative complications for analysis

Parameters	Definitions
Hospital stay	Days from initial operation to hospital discharge plus any readmission within 30 days
Console time	Time of console surgeon activity (min)
Postoperative hemorrhage	Evidence of blood loss from drains, based on ultrasonography or CT
Transfusion rate	The number of blood transfusions
Urinary leakage	Evidence of creatinine level > 500 μmol/l and volume of the drain output exceeds 200 ml/24 h, confirmed on cystography
Lymphorrhea	Evidence of creatinine level < 500 μmol/l, hematocrit < 0.2, and volume of the drain output exceeding 200 ml/24 h, no urinary leakage on cystography
Intraabdominal fluid collection	Collection of fluid measuring ≥ 3 cm associated with clinical or laboratory abnormalities
Symptomatic fluidothorax	Fluid in the pleural cavity associated with respiratory distress or a need to evacuate the fluid
Thromboembolism	Unilateral limb swelling, acute respiratory insufficiency, based on ultrasonography or CT
Myocardial infarction	Increase of serum concentration of CK-MB and troponin and/or the following ECG changes: new Q waves ≥ 0.04 in duration, new persistent ST elevation, and/or depression
Brain stroke	Presence of neurological symptoms, findings on CT scan or MRI
Pneumonia	Presence of a new infiltrate on chest X-ray, as well as the following: body temperature > 38 °C, abnormal elevation of WBC, or positive sputum, and requiring antibiotic treatment
Acute renal failure	Serum creatinine > 300 μmol/l and/or need for dialysis
Wound infection	Surgical site infection associated with laparotomy that develops during the initial hospital stay

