Urinary tract infection	Culture-positive urine, pyuria, or bacteriuria on urinalysis requiring antibiotic treatment

*CK-MB* creatine kinase MB isoenzyme, *ECG* electrocardiogram, *WBC* white blood cells, *CT* computer tomography, *MRI* magnetic resonance imaging

Postoperative complications are graded based on severity according to the Clavien-Dindo definition (Table 2) [33].

**Table 2 Tab2:** Complication grades according to the Dindo-Clavien classification scheme

Grade	Definition
Grade I	Any deviation from the normal postoperative course without the need for pharmacological treatment or surgical, endoscopic, and radiologic intervention
Grade II	Requiring pharmacological treatment with drugs other than those allowed for grade I complications
Grade III	Requiring surgical, endoscopic, or radiological intervention
Grade IIIa	Intervention not under general anesthesia
Grade IIIb	Intervention under general anesthesia
Grade IV	Life-threatening complications requiring intensive care unit management
Grade IVa	Single-organ dysfunction
Grade IVb	Multiorgan dysfunction
Grade V	Death of the patient

We plan to seek for adverse events with repetitive blood sampling and imaging to prevent the underreported frequency of these events. But we are aware that the incidence is low, and our data will might not have sufficient power to make a definitive conclusion about safety.

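### The tests described in the text cannot establish infarction, thromboembolism or stroke as Table 1 defines them, and the window for detailed adverse event recording is undefined

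*Protocol article*

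**What the plan says.** The additional endpoint is to confirm the safety of tranexamic acid. Primary and secondary endpoints lists complications of interest, "especially analyzing the incidence of cardiac events and venous thromboembolism (VTE) after the procedure", and says below Table 2: "We plan to seek for adverse events with repetitive blood sampling and imaging to prevent the underreported frequency of these events". The next sentence accepts that incidence is low and that power may be too small for a firm safety conclusion.

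On tests, Data collection states: "Laboratory tests will include blood cell count (BCC), hematocrit test, and plasmatic creatinine level at the beginning of the procedure", with repeats at 3–6 h, POD 1, POD 2 and POD 7. The only imaging that the text schedules for all patients is on POD 7, when, according to Study treatment, "the blood sampling and ultrasound of the lower abdomen will be performed".

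On recording, Adverse event reporting and harms first says that events reported by patient or investigator are recorded and CTCAE-scored, with no time limit. It then states: "If AE happen during the experimental treatment period, all the details will be notified in the CRF". The details meant are onset, clinical picture, severity, duration and causality. The period is not defined. Study treatment describes a single dose in 100 ml saline at the beginning of the procedure.

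**The concern.** The article makes a specific claim about how harms will be found, and that claim needs to match the schedule. The events singled out are the ones a reader would worry about with an antifibrinolytic, and the Discussion itself raises the thromboembolic question. If the sampling and imaging described cannot identify them, the sentence lends the safety results a protection they do not have for those events. The caveat that follows does not repair this, because it concedes low power and not incomplete ascertainment.

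The recording window raises a related problem. With one infusion and 3 months of follow-up, sites could differ on whether an event in week 4 needs an onset date and a causality judgment. Both are needed to interpret a handful of late events.

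**Working it through.** The plan gives no figure for safety ascertainment, so there is nothing to reproduce. The check sets Table 1 against the tests and visits in the text.

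**Step 1: definitions against scheduled tests.**

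| Event | What Table 1 needs | Scheduled for all patients in the text? |
|---|---|---|
| Myocardial infarction | CK-MB and troponin rise and/or ECG changes | No |
| Thromboembolism | "Unilateral limb swelling, acute respiratory insufficiency, based on ultrasonography or CT" | No; the POD 7 ultrasound is of the lower abdomen |
| Stroke | Neurological symptoms, CT or MRI findings | No |
| Acute renal failure | Creatinine above 300 μmol/l and/or dialysis | Yes, serial creatinine |
| Postoperative hemorrhage | Blood loss from drains, ultrasound or CT | In part: drain volume, blood counts, ultrasound |
| Intraabdominal collection | At least 3 cm, with clinical or laboratory abnormality | In part: POD 7 ultrasound, blood tests |

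The sampling and imaging claim therefore has support for the last three rows and none for the first three.

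**Step 2: what does capture the first three.** The text gives a daily visit by an investigator or delegate, discharge on POD 2, an attendance on POD 7 and a visit at 3 months. Data collection also gathers readmissions with reasons, and reinterventions. Health economic analysis gathers readmissions, emergency attendances and outpatient attendances at t5. These routes work through symptoms and reports. For thromboembolism and stroke that suits the definition, which includes symptoms. Infarction can meet its definition without symptoms, and a silent one would need a test that the text does not schedule.

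**Step 3: the recording window.**

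| Item for an event after the treatment period | Covered by a rule without a time limit? |
|---|---|
| Recording and severity | Yes: CTCAE scoring; complications also graded by Clavien-Dindo |
| Causality, serious event | Yes: imputability must be established |
| Causality, non-serious event | No |
| Onset, signs, duration | No |
| Follow-up to resolution | Yes: Ancillary and post-trial care |

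**Step 4: context on size.** The inputs are 200 patients at 1:1, so 100 per arm, and the Discussion's thromboembolic range for robotic surgery, 0.2–3.7%. Expected events per arm are n × p: 100 × 0.002 = 0.2 and 100 × 0.037 = 3.7.

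Rough power to detect a doubling at two-sided 5% is Φ{[(p₂ − p₁)√n − 1.96√(2p̄q̄)] / √(p₁q₁ + p₂q₂)}.

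- For 0.2% against 0.4%: (0.020 − 0.152)/0.077 = −1.70, so about 4%.
- For 3.7% against 7.4%: (0.370 − 0.635)/0.323 = −0.82, so about 21%.

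The normal approximation is crude at such counts. These figures show that the comparison is uninformative even with complete capture. They do not estimate missed events.

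**The case against.** The strongest reply is that a reader might infer that nothing in the plan can detect these events, and that this is wrong. It is wrong: the daily, POD 7 and 3-month visits can pick up symptomatic events and prompt diagnostic tests, and attendances and readmissions are already asked about. The sentence on sampling and imaging also speaks of adverse events in general, and the scheduled tests do serve several outcomes in Table 1.

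A reader might also take the treatment period to mean the infusion alone, leaving a late event with no recording instruction. The text does not support that. The term is undefined, and general recording, severity scoring, imputability of serious events and follow-up to resolution carry no such limit.

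Two numbers are tempting. From POD 7 to about day 90 is 83 of 90 days without a scheduled contact, but that says nothing about how many events go unreported. Nor can one missed event be put at a quarter to all of an arm's count. Against 3.7 expected events it is 1/3.7, or 27%; against 0.2 it is five times the expectation.

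Finally, this is a condensed article and Fig. 2 is not available here. Its legend shows no time point between POD 7 and 3 months, but the figure could list further tests at the visits. That reservation stands, and the sponsor could settle it by pointing to them. Assessors are blinded, and nothing suggests that missed events would differ between arms.

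What remains is that a stated safeguard does not reach the events the protocol emphasizes, and that a recording window is badly fixed.

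**Conclusion.** The point holds in a limited form. On the tests described in the text, the statement about preventing under-reporting is not supported for infarction, thromboembolism or stroke, whose detection is driven by symptoms and reports. The window for detailed recording is undefined and fits poorly with a single infusion and 3 months of follow-up. The loss is mainly onset, signs and duration for late events, and causality for late non-serious ones.

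The effect is on how firmly the safety results can be read. No bias between arms is shown, and the hemoglobin endpoint is not touched. The document allows no numerical estimate of missed events. The conclusion assumes that Fig. 2 adds no cardiac markers, ECG or vascular or brain imaging.

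**What to change.** 1. In Primary and secondary endpoints, limit the statement on sampling and imaging to the outcomes that the scheduled tests can detect, and say that infarction, VTE and stroke are reported as clinically recognised events. If Fig. 2 schedules relevant tests, name them in the text instead.
2. In Adverse event reporting and harms, replace the undefined period with: from start of infusion to the t5 visit.
3. At the existing POD 7 and t5 visits, ask every patient the same short list (leg swelling, breathlessness, chest pain, neurological symptoms). Use the attendance and readmission data already collected for the cost analysis to identify events.

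The cost is protocol and CRF wording, a few minutes at two existing visits and a more modest safety claim. No new procedure is needed.

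Timing matters. Trial status expected the last patient by February 1, 2022, which puts the last 3-month visit near May 1, 2022, before the article appeared on June 18, 2022. Item 3 therefore helps only patients whose visits are still to come. Item 1 and the use of attendance data remain open to the sponsor in any case. For completed visits, onset and causality under item 2 could be added only as far as source records allow.

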## Methods for avoiding bias

### Minimizing systemic bias

Participants will be randomly allocated to one of the groups before the surgical procedure after meeting the eligibility criteria with a ratio of 1:1. Operating surgeons, attending physicians, nursing staff, and outcome assessors will be blinded. The randomization process will follow the CONSORT guidelines (Fig. 1) [34].

**Fig. 1 Fig1:**
[figure not shown]
Process phases flowchart of randomized trial according to the CONSORT guidelines

Standard Protocol Items: Recommendations for Interventional Trials (SPIRIT) 2013 Checklist was used to improve the quality of the study protocol [35] (Fig. 2).

**Fig. 2 Fig2:**
[figure not shown]
The schedule of enrollment, interventions, and assessments of randomized trial according to the SPIRIT guidelines (*t*_−2_ = − 14 − 1 days; *t*_−1_ = − 1 day; *t*_0_ = at the beginning of the procedure; *t*_1_ = 3 h after the procedure; *t*_2_ = POD1; *t*_3_ = POD2; *t*_4_ = POD7; *t*_5_ = 3 months after the procedure ± 7 days)

### Minimizing treatment bias

Administration of tranexamic acid at the beginning of the procedure by an anesthesiologist is a simple common procedure, performed on a routine basis, which eliminates a learning curve.

All patients will undergo robotic-assisted radical prostatectomy without pelvic lymphadenectomy using the same technique. All surgeons participating in the study are familiar with this procedure. The dorsal vein complex (DVC) will be sutured at the beginning of the procedure.

### Minimizing measurement bias

Measurement of hemoglobin level drop and detection and grading of postoperative complications will be based on data in the patient’s record form. Patient and clinical investigators or a delegated physician will be blinded.

## Statistical methods

Each patient’s allocation to the analyzed population will be defined prior to the analysis and will be documented. In the full analysis set, patients will be analyzed as randomized according to the intention-to-treat principle. The intention-to-treat principle implies that the analysis includes all randomized patients. The per-protocol analysis set will include all the patients without major protocol deviation. Deviations from the protocol will be assessed as major or minor. Patients with major deviations from the protocol will be excluded from the protocol analysis. The safety analysis set will analyze the patients according to the treatment. The null hypothesis assumes that there is no difference in the hemoglobin level drop after the procedure in both groups. We will use a two-sample *T* tests allowing unequal variance with respect to the endpoint, which is the drop of hemoglobin levels. Differences between age and PSA will be assessed by the non-parametric Mann-Whitney *U* test. BMI and specimen weight will be compared by the Kolmogorov-Smirnov test. A *P*-value < 0.05 will be considered statistically significant. Statistical analyses will be performed using the NCSS statistical software (NCSS, Kaysville, UT, USA).

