## Methods/design

The RARPEX trial is designed as a randomized, placebo controlled, surgeon- and patient-blinded superiority single-center study with two parallel groups. Randomization will be performed as a block randomization with 1:1 allocation.

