### Objectives and hypothesis

The primary aim of the Robotic **A**ssisted Radical Prostatectomy with EXacyl (RARPEX) trial is to investigate the effect of tranexamic acid on perioperative and postoperative blood loss (decrease in hemoglobin levels) in robotic-assisted radical prostatectomy.

H0: The drop of hemoglobin level after the procedure is similar in both groups.

HA: The drop of hemoglobin level after the procedure in control group is higher than in study group.

Additional endpoint of the RARPEX trial is to analyze the effect of tranexamic acid on postoperative complications and confirm the safety of tranexamic acid in robotic assisted radical prostatectomy.

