### Sample size calculation

The sample size calculation is based on the data from our pilot study [29]. We used two-sample *T* tests allowing unequal variance with respect to the primary endpoint, which is the difference in hemoglobin level drop on postoperative day (POD) 1. The level of significance is set to 5 g. With *α* = 1% and *β* = 10%, a sample size of 64 patients per group is necessary to detect a clinically significant difference between the groups. With an expected dropout rate over 33%, we plan to enroll 200 patients in the study.

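### The primary comparison is sized at alpha 1% but will be declared significant at P < 0.05, and neither level is stated as one- or two-sided

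*Protocol article*

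**What the plan says.** Sample size calculation (protocol article) bases the size on two-sample t "tests allowing unequal variance with respect to the primary endpoint, which is the difference in hemoglobin level drop on postoperative day (POD) 1". It continues: "With *α* = 1% and *β* = 10%, a sample size of 64 patients per group is necessary".

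Statistical methods names the same test for the haemoglobin drop, then lists comparisons of age, PSA, BMI and specimen weight, and closes with the only analysis threshold in the article: a P "value < 0.05 will be considered statistically significant".

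Objectives and hypothesis gives a directional alternative: "The drop of hemoglobin level after the procedure in control group is higher than in study group". The null is worded as "The drop of hemoglobin level after the procedure is similar in both groups". Statistical methods restates it: "The null hypothesis assumes that there is no difference in the hemoglobin level drop after the procedure in both groups". Methods/design calls the trial a "surgeon- and patient-blinded superiority single-center study with two parallel groups".

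Interim analyses says that none is planned. No multiplicity rule is given. Nowhere does the article say whether the 1%, the 0.05 or the t test is one- or two-sided.

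**The concern.** The level used to size a trial and the level used to judge its primary result should be the same. Here they differ by a factor of five, and nothing in the article explains the gap: no interim look spends alpha, and no adjustment for several endpoints is described.

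The article therefore supports two decision rules for one primary endpoint. If the choice is left until the data are seen, a P of 0.03 can be reported as a success by citing Statistical methods or as a failure by citing Sample size calculation. The unstated sidedness adds to this, because a directional alternative can be read as calling for a one-sided test at either level. The stated basis for 64 per group also does not describe the test that will be run.

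**Working it through.** **Inputs.** Alpha 1%, beta 10%, 64 per group (Sample size calculation). Threshold 0.05 (Statistical methods). Candidate design differences: 5 g (Sample size calculation, read here as g/l), 10 g/l (Primary and secondary endpoints; Discussion, Blood loss) and the pilot's 8 g/l (Discussion, Blood loss). No SD is given, so 64 per group cannot be reproduced directly. The SD is back-solved and is an assumption throughout.

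**Step 1: false-positive rate.** With matching sidedness the ratio is 0.05/0.01 = 5. In the direction of the alternative hypothesis, each level is divided by its number of sides:

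| Planned 1% | Tested 5% | Planned error | Error at analysis | Ratio |
|---|---|---|---|---|
| two-sided | two-sided | 0.5% | 2.5% | 5 |
| one-sided | one-sided | 1% | 5% | 5 |
| two-sided | one-sided | 0.5% | 5% | 10 |
| one-sided | two-sided | 1% | 2.5% | 2.5 |

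A simulation of the unequal-variance t test under the null (64 per group, 100,000 runs) gave rejection rates of 1.0% at two-sided 0.01 and 5.0% at two-sided 0.05, so the test itself holds its level.

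**Step 2: design effect implied by 64 per group.** Take the 1% as two-sided. By normal approximation, the standardised difference is (2.576 + 1.282)/√(64/2) = 3.858/5.657 = 0.682. With the noncentral t (126 df) it is 0.691, which is used below. The implied SD is the design difference divided by 0.691: 7.2 for 5 g/l, 11.6 for 8 g/l and 14.5 for 10 g/l.

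**Step 3: observed differences whose verdict changes.** The smallest significant difference is t × SD × √(2/64), with t = 2.615 at two-sided 1%, t = 1.979 at two-sided 5%, and √(2/64) = 0.1768. Unrounded SDs are used.

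| Sized on | SD | Needed at 5% | Needed at 1% |
|---|---|---|---|
| 5 g/l | 7.2 | 2.5 g/l | 3.3 g/l |
| 8 g/l | 11.6 | 4.1 g/l | 5.4 g/l |
| 10 g/l | 14.5 | 5.1 g/l | 6.7 g/l |

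Any result between the last two columns is positive under one section and negative under the other. With 64 per group, P falls in that zone in about 7% of trials if the true effect equals the design effect, and in about 23% if it is half of it.

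**Step 4: power at 5%.** By normal approximation, 3.858 − 1.960 = 1.898, which gives 97.1%; the noncentral t gives 97.3%. For 90% power at two-sided 5%, the t-based size is 45 per group (46 by normal approximation). These figures do not depend on which difference was used. If the 1% was one-sided instead, the standardised difference is 0.645. Power at 64 per group is then about 95% at two-sided 5%, and 52 per group would give 90%.

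**The case against.** The strongest defence is that 0.05 is the only decision threshold in the article and a conventional one. Sizing at a stricter level than the one tested does no harm to validity: the type I error is held at 5% and power rises. That stands. It means the fault is an inconsistency between planning and analysis, not an uncontrolled error rate, and it does not show that 1% is the level that should govern.

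It might also be said that the 0.05 sentence belongs to the baseline comparisons it follows. Nothing limits it to them. If it were so limited, the article would give no analysis threshold for the primary test at all. A separate analysis plan could choose one level, but both figures would still stand in print.

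Some stronger readings are tempting and are not supported:

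- **That the false-positive risk is at least five times the planned one.** Five is not a lower bound: if the 1% was one-sided and the 0.05 is two-sided, the ratio in the direction of the alternative is 2.5.
- **That it is ten times the planned two-sided 1%.** That mixes one tail with two. Ten comes only from comparing 5% with the 0.5% in one tail; the total error would still be 5% against 1%.
- **That the directional alternative clashes with a no-difference null.** This is a conventional pairing in a superiority trial and inflates nothing. Only the unstated sidedness is at fault.
- **That the g/l zone can be given as a single range.** The article offers 5, 8 and 10 g/l and no SD, so only the set of ranges above is supportable.

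**Conclusion.** Wrong as written. The article fixes two different significance levels for one primary test and leaves the sidedness of both open. With matching sidedness the type I error at analysis is 5% against the planned 1%, and in the direction of the alternative the ratio lies between 2.5 and 10. The practical effect is a band of results with no agreed verdict: P between 0.01 and 0.05, which at 64 per group means observed differences of 2.5 to 3.3, 4.1 to 5.4 or 5.1 to 6.7 g/l, according to the design difference.

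The g/l figures rest on an SD back-solved under a two-sided 1% and 90% power. The factor of five and the disputed P range rest on no assumption about the SD.

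**What to change.** Before unblinding, state one alpha and its sidedness for the single primary test, in the same words in Sample size calculation and Statistical methods, and make the test match the alternative in Objectives and hypothesis. Two options resolve the conflict:

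- **(a) Keep 1% for the primary test, as sized.** P < 0.05 then applies only to the other comparisons, as a nominal level.
- **(b) Keep 0.05 for the primary test.** Restate the sample size justification accordingly: about 97% power at 64 per group if the 1% used for sizing and the 0.05 are both two-sided.

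The article does not settle which was intended, so the sponsor must choose.

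The cost is a short text change and no extra patients. Option (a) keeps the planned 90% power only at the design difference. If the trial was sized on 10 g/l (SD 14.5) and the true difference is the pilot's 8 g/l, power at 64 per group is about 70% at two-sided 1% against 87% at two-sided 5%. Option (b) accepts a higher false-positive rate than the one planned. Either may have to go through the ethics committee and IRB route described under Protocol amendments.
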